### Outcomes

Outcomes include mortality, CVD and cardiovascular mortality, serial creatinine (to determine eGFR trajectory and chronic kidney disease) and other laboratory measures, pregnancy outcomes and complications, and development of diseases that frequently lead to CKD (e.g., hypertension, DM, and obesity). Outcomes will be ascertained from national registries, medical record review of donors and REP controls, and a new survey administered to both donors and controls. A list of data collected, data source, and frequency of data collection is provided in Table 2 and is summarized below.

**Table 2 Tab2:** Data collection sources and frequency for REP controls and UMN donors. CR: Chart Review, DS: Donor survey + chart review if available (every 3 years), SS: Study Survey, LD: Lab data (every year)

	Source of data	
Data	UMN Donors	REP Controls

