**Outcomes**		
CVD^6^	DS, SS	CR, SS
Diabetes	DS, SS	CR, SS
Cancer	DS, SS	CR, SS
Hematuria	DS, SS	CR, SS
High cholesterol treated with medication	DS, SS	CR, SS
Hypertension treated with medication	DS, SS	CR, SS
Pregnancy history^7^	DS, SS	CR, SS
Proteinuria	DS, SS	SS
Kidney disease/ abnormal kidney function/ ESKD	DS, SS, USRDS	CR, SS, USRDS
Vital status and cause of death	DS, SS, NDI	CR^8^, SS, NDI

^1^ Chart review for controls includes abstraction of data from electronic transfer from the Rochester Epidemiology Project (REP) database, Mayo clinic paper records, Olmstead Medical Center electronic and paper record, Olmstead Community Hospital electronic and paper records, Epic, and the REP browser (electronic record system) from date of first REP encounter to date of last follow-up

^2^Permissible substance abuse at donation/donation is defined as a remote history of marijuana use with no active use around the time of the donation date or current marijuana use as long as it does not interfere with lifestyle. Remote other substance use is not a contraindication to donation as long as its truly remote

^3^Permissible depression/anxiety at donation/donation is defined as well controlled, in the distant past prior to the donation date, or involving few episodes of care

^4^Permissable hypertension at donation/donation includes that which is well controlled (< 140/90), treated with a diuretic antihypetensive agent, a non-diuretic antihypertensive agent, or both (1 diuretic and 1 non-diuretic hypertensive agent), age needs to be > 50 years. Exclude if age < 50 years or not well controlled or using 2 or more non-diuretic agents or using 2 or more diuretic agents

^5^Urine Dipstick, 24 H Urine Protein, Urinalysis Predicted 24-Hour Protein, Protein-Osmolality Ratio, Urine Protein to Creatinine Ratio, Urine Albumin to Creatine Ratio, 24 H Urine Albumin

^6^Congestive heart disease, myocardial infarction, cerebrovascular accident, transient ischemic attack, angioplasty, stents

^7^Number and year of pregnancies, pregnancy outcome (singleton, twins, triplets, ≥ 4, abortion, miscarriage, fetal death), gestational length (full term, pre-term), and pregnancy complications (gestational hypertension, gestational diabetes, proteinuria, eclampsia, preeclampsia)

^8^Proof of life noted for medical encounters with no data

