#### National registries: mortality and ESKD

To determine mortality/causes of death and ESKD, patient identifiers (name, birthdate, social security number, address) for the UMN and Mayo donors and the REP controls will be sent in a secure manner to the NDI and to the USRDS, respectively.

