#### Survey data: mortality, ESKD, and other outcomes

UMN donors and validated REP controls not known to be deceased will be sent a standardized survey to determine outcomes. This survey is based on the existing survey that has been used for UMN donors, but modified to be usable with both LDs and controls. This survey supplements the capture of key data that may not be consistently documented in the medical record with specific items including: hematuria or proteinuria of at least 6 months duration, hypertension, DM, heart failure, myocardial infarction, angioplasty or stent, angina, smoking history, and pregnancy history; and family history of hypertension, DM, or ESKD (see **Supplemental Materials** for the survey). We will additionally capture cancer information to use as a negative control (see statistical analysis section).

The survey will allow for uniform ascertainment of outcomes between UMN donors and REP controls. Because Mayo LDs have not been routinely contacted about health outcomes after donation, they do not have a similar long-term follow-up history as UMN LDs from which to validate survey responses. Because of this and budgetary constraints, only the REP controls and UMN donors will be surveyed.

UMN donors will be contacted to complete the survey using a similar process as described previously for the 3-year postdonation follow-up surveys. Data obtained from this new survey will be used to supplement data collected in the triannual surveys sent to UMN donors previously.

For REP controls, mailing addresses and phone numbers will be obtained from recent Olmsted County medical care episodes. REP controls without a recent medical visit will be queried in Accurint™ to determine if they are alive and if so, identify their most recent mailing address and phone number. Up to three mailed surveys, with the first including an incentive item for participation, will be sent to the controls followed by up to 5 phone calls (including evenings and weekends). After surveying the first validated control for each REP donors, we will prioritize surveying controls for donors who lack completed surveys by a matched control.

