#### Statistical analyses details

Log-rank tests and Kaplan Meier curves will be used as preliminary assessments to compare the risk of all-cause mortality and cardiovascular mortality, CVD, ESKD, CKD (eGFR < 45; eGFR < 30 ml/min/1.73m^2^), proteinuria, DM, and hypertension after index date between LDs and healthy controls. Our study is powered based on these analyses. Cox proportional hazards models will also be used to test for an increased risk of adverse outcomes in living LDs versus controls while directly accounting for the variables used for matching (to account for any possible residual imbalance between the cohorts similar to how one may adjust for characteristics in a randomized controlled trial to account for residual imbalance and to improve efficiency). In analyses involving Mayo LDs and their associated controls we will account for donation center (Mayo vs. UMN) as a covariate in the model. If the proportional hazards assumption fails, an alternative method such as an accelerated failure time model will be considered. Indeed, the risk of mortality and ESKD may disproportionately increase with long-term follow-up on the 60-year scale of this study [123, 130, 131]. A similar approach will be used to test for increased risk of outcomes for LDs versus controls after development of DM, hypertension, proteinuria, de novo kidney disease, or pregnancies with gestational hypertension or preeclampsia, but additional measures (e.g. matching, adjustment) will be used to account for the time of disease onset.

In order to evaluate biases in the selection of controls and ascertain outcomes, we will compare the risk of non-kidney-related cancer between donors and controls using the previously described methods. As cancer risk is lower in donors than the general population, we expect a similar lower risk in controls [150]. If controls are well matched, we do not expect the risk of non-kidney related cancer to differ between donors and controls. If a difference in cancer risk is identified, it may indicate imbalance in our matching and it will be further investigated using methods described in Shi et al. [151].

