#### Power

Given the results identified using preliminary matching algorithms and chart review we assume that we will be able to identify 3 controls for 98% of LDs and at least one of those controls will be included in a more restrictive matched subset (i.e., known presence of CKD, known serum creatinine/urine protein at or prior to index date). For the following power analyses, the type-1 error probability is set to 5%.

For estimating the minimal detectible hazard ratio for all-cause mortality, we note that at present, 12% of UMN LDs, 7% of all Mayo LDs, and 11% of identified preliminary controls are deceased. With a mortality rate of 11% in our study population, we estimate that our minimal detectible hazard ratio with 80% power will be 1.13 for a 3:1 matching and 1.16 for a 1:1 matching.

In UMN LDs, approximately 13.5% have developed eGFR < 45 ml/min/1.73m^2^ during follow-up. In our analysis comparing the risk of developing an eGFR < 45 between UMN LDs and healthy controls, we conservatively estimate that eGFR < 45 will develop in approximately 8 to 14% of our study population. With this assumption, our minimal detectable hazard ratio will be between 1.20 and 1.15 for a 3:1 matching and between 1.25 and 1.18 for a 1:1 matching.

Among the 301 UMN LDs who developed DM after donation without first developing CVD, 57 individuals (19%) later developed CVD. Assuming identification of a 1:1 match for approximately 80% (240) of these donors and that the overall proportion of individuals in our study population who develop CVD after DM ranges from 15 to 23%, we will have 80% power to detect a hazard ratio between 1.94 and 1.70.

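### CVD is ascertained from unequal sources without NDI cardiovascular deaths, so fatal first events can be lost, plausibly more often in donors than in controls

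*Protocol article*

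**What the plan says.** All places are in the protocol article.

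- **Sources for CVD.** The row in Table 2 (Outcomes) reads "CVD^6^ DS, SS CR, SS": donor survey and study survey for UMN donors, chart review and study survey for REP controls. By the table's legend, the donor survey code includes chart review where available, on a 3-yearly cycle.
- **Components.** Footnote 6 lists "Congestive heart disease, myocardial infarction, cerebrovascular accident, transient ischemic attack, angioplasty, stents". It neither restricts these to non-fatal events nor names cardiovascular death.
- **Registries.** Table 2 adds USRDS to the kidney disease/ESKD row and NDI to the row "Vital status and cause of death". The section on national registries confirms the linkage for UMN donors, Mayo donors and REP controls: "To determine mortality/causes of death and ESKD, patient identifiers" are sent to the two registries.
- **Outcomes and analysis.** "Outcomes include mortality, CVD and cardiovascular mortality" are listed side by side. Under Statistical analyses details, Kaplan-Meier curves and log-rank tests, followed by Cox models, are to "compare the risk of all-cause mortality and cardiovascular mortality, CVD, ESKD" and other endpoints.
- **Timing of capture.** "UMN donors and validated REP controls not known to be deceased will be sent a standardized survey to determine outcomes". Under Medical record review, UMN donor records are abstracted when the survey is administered. Footnote 1 to Table 2 has control charts abstracted from first REP encounter to last follow-up.
- **Claim of uniformity.** The Discussion paragraph on event ascertainment says that events are obtained by the same approach in both groups and that this avoids differential ascertainment bias.

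**The concern.** A person who dies of a first infarction or stroke cannot answer a later survey. In a UMN donor the event then reaches the CVD endpoint only if an available chart supplies it, and those charts are collected around survey contacts. In a control treated at a REP hospital the same event is in the linked inpatient record and meets footnote 6. The one source that treats both groups alike for fatal events, NDI cause of death, is not listed for CVD.

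Under the planned time-to-event methods, a cardiovascular death with no recorded CVD event would ordinarily be censored at death. If that happens more often in donors, the CVD hazard ratio is pulled toward no excess. CVD is part of aim (b), and CVD after diabetes is one of the three comparisons with a power figure; in UMN donors that figure starts from 301 people with diabetes, of whom "57 individuals (19%) later developed CVD". A bias in this direction would make donation look safer than it is on an outcome that the Background describes as disputed.

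**Working it through.** **1. The plan's own CVD figure.** The only power figure for CVD is for CVD after diabetes: 240 pairs, 1:1, 15 to 23% with CVD, 80% power, type I error 5%, detectable hazard ratio 1.94 to 1.70. With Schoenfeld's formula, two-sided,

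HR = exp[(1.960 + 0.842) / √(0.25 × D)]

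- D = 480 × 0.15 = 72: HR = 1.935
- D = 480 × 0.23 = 110.4: HR = 1.704

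The inputs agree as well: 57/301 = 18.9% and 0.8 × 301 = 241. The power arithmetic is right. It does not bear on ascertainment.

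**2. Is the missing NDI only table shorthand?** Table 2 names USRDS in the ESKD row and NDI in the cause-of-death row. It names a registry where the registry feeds an outcome, so its absence from the CVD row reads as part of the stated sources.

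**3. Capture of a fatal first event, side by side.**

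| | UMN donors | REP controls |
|---|---|---|
| Survey | Donor survey (intermittent before 2003, then at set intervals, eventually 3-yearly); new survey only if not known dead | New survey only if not known dead |
| Chart | If available, abstracted at survey administration | Linked record to last follow-up, including inpatient stays at affiliated hospitals |
| NDI cause of death | Requested, not listed for CVD | Requested, not listed for CVD |

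From Table 1, 99 + 658 + 796 + 1,040 = 2,593 of 4,022 UMN donors (64%) donated before 2000, so part of their follow-up precedes the regular survey cycle. Also, 9.5% returned no survey.

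**4. Effect on the hazard ratio.** Let f be the share of first CVD events that are fatal, and c_d and c_c the shares of those captured in donors and controls. None of the three is in the document. With low incidence and no false positives,

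HR observed = HR true × [1 − f(1 − c_d)] / [1 − f(1 − c_c)]

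For a true HR of 1.20:

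| Assumed capture | f = 10% | f = 20% | f = 30% |
|---|---|---|---|
| Equal in both groups | 1.20 | 1.20 | 1.20 |
| None in donors, half in controls | 1.14 | 1.07 | 0.99 |
| None in donors, all in controls | 1.08 | 0.96 | 0.84 |

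Example, second row, f = 20%: 1.20 × 0.80/0.90 = 1.07. Zero donor capture is the extreme for any given f and c_c. With a quarter captured in donors and half in controls at f = 20%, the result is 1.20 × 0.85/0.90 = 1.13. If controls were the worse-captured group, the ratio would move the other way: half in donors, none in controls, f = 20% gives 1.20 × 0.90/0.80 = 1.35.

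**5. Effect of adding NDI deaths on precision.** If the plan's 15 to 23% excludes fatal first events (not stated), the event count becomes D/(1 − f) and the detectable HR for CVD after diabetes falls:

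| f | 15% | 23% |
|---|---|---|
| As planned | 1.935 | 1.704 |
| 10% | 1.871 | 1.658 |
| 20% | 1.805 | 1.611 |
| 30% | 1.738 | 1.562 |

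**The case against.** Several objections have force.

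- **Fatal CVD is already tested.** Cardiovascular mortality is a named outcome with NDI cause of death in both groups, and reporting it apart from CVD is a recognised choice. This stands as far as it goes. It does not repair the hazard ratio for CVD or for CVD after diabetes, which rest on the unequal sources.
- **Donor capture is not zero.** Donor charts are used where available, other clinics can be contacted with permission, and Table 2 lists the donor survey as a source for vital status and cause of death. This stands. The rows with no donor capture are limiting cases.
- **Controls lose events too.** Eligibility needs only one REP encounter a year or more after index, and matching may be broadened to people with unknown or outside residence. Deaths outside the REP area can be missed. Sudden cardiac death is not in footnote 6, so it would be lost in both groups. This stands, and it makes the net direction plausible but not proven.
- **The detail belongs in an analysis plan.** How to treat a cardiovascular death as a competing event can fairly be left there. The sources, the component list and the uniformity claim, however, are stated in this article and do not fit together.

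A reader might infer that the endpoint is limited to non-fatal events, or that the plan counts such donors as CVD-free. Neither is written: a fatal infarction found in a chart meets footnote 6, and the handling of cardiovascular deaths is not described. Nor does the study hypothesise no excess; it expects a slight, clinically insignificant increase.

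**Conclusion.** The point holds in a limited form. As written, the plan can lose fatal first CVD events that the NDI could supply, and its sources make that loss plausibly greater in UMN donors than in controls. For CVD, the Discussion's statement that both groups are ascertained the same way is not supported by Table 2.

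It would go too far to say that the CVD harm is understated. Omitting the NDI does not by itself bias the relative effect: equal loss lowers the absolute incidence and the risk difference but leaves the hazard ratio about unchanged, unless donation raises fatal events more than non-fatal ones. A bias toward no excess needs poorer capture in donors. On the assumptions of 10 to 30% fatal first events, none captured in donors and half in controls, a true hazard ratio of 1.20 appears as about 1.14 to 0.99. The document gives none of these values, so this range illustrates the possible size and does not estimate it. The change is worth making because the data are already being obtained.

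**What to change.** - Define the CVD outcome, overall and after diabetes or hypertension, as the first of a footnote 6 event or an NDI-coded cardiovascular death, in donors and controls alike. Add NDI to the CVD row of Table 2.
- Keep the diagnosis-only version as a secondary analysis, and keep cardiovascular mortality as its own outcome.
- Qualify the Discussion's uniform-ascertainment statement for CVD. The change equalises the source for fatal events only; non-fatal events would still come from donor surveys and available charts on one side and full chart review on the other.

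The cost is about a sentence in the outcome definition and one in the Discussion, with no new data request. The downsides are some misclassification from death-certificate coding, drawn from the same source in both groups, and a slightly broader estimand. The retained secondary analysis shows how much the broader definition matters.

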#### National registries: mortality and ESKD

To determine mortality/causes of death and ESKD, patient identifiers (name, birthdate, social security number, address) for the UMN and Mayo donors and the REP controls will be sent in a secure manner to the NDI and to the USRDS, respectively.

#### Medical record review: mortality, ESKD, and other outcomes

Once a control is validated, as noted above, abstractors collect follow-up data from the medical record. Lab measures obtained after index are limited to up to one value per calendar year and include: weight, blood pressure, serum creatinine, serum glucose, BUN, serum creatinine, and urine protein. For efficiency of abstraction, the database is prefilled with all electronically available values from the medical record and then validated by the abstractor. Finally, clinical diagnoses and the year they occurred are recorded from the medical record.

As described above, when UMN LDs are surveyed, they are also asked to provide recent lab test results and copies of medical records. At the time of survey administration, abstractors collect follow-up data from medical record of the UMN health system and affiliated clinics. With LDs’ permission, UMN investigators will contact other clinics for recent medical records that include clinical notes and laboratory test results.

#### Survey data: mortality, ESKD, and other outcomes

UMN donors and validated REP controls not known to be deceased will be sent a standardized survey to determine outcomes. This survey is based on the existing survey that has been used for UMN donors, but modified to be usable with both LDs and controls. This survey supplements the capture of key data that may not be consistently documented in the medical record with specific items including: hematuria or proteinuria of at least 6 months duration, hypertension, DM, heart failure, myocardial infarction, angioplasty or stent, angina, smoking history, and pregnancy history; and family history of hypertension, DM, or ESKD (see **Supplemental Materials** for the survey). We will additionally capture cancer information to use as a negative control (see statistical analysis section).

The survey will allow for uniform ascertainment of outcomes between UMN donors and REP controls. Because Mayo LDs have not been routinely contacted about health outcomes after donation, they do not have a similar long-term follow-up history as UMN LDs from which to validate survey responses. Because of this and budgetary constraints, only the REP controls and UMN donors will be surveyed.

UMN donors will be contacted to complete the survey using a similar process as described previously for the 3-year postdonation follow-up surveys. Data obtained from this new survey will be used to supplement data collected in the triannual surveys sent to UMN donors previously.

For REP controls, mailing addresses and phone numbers will be obtained from recent Olmsted County medical care episodes. REP controls without a recent medical visit will be queried in Accurint™ to determine if they are alive and if so, identify their most recent mailing address and phone number. Up to three mailed surveys, with the first including an incentive item for participation, will be sent to the controls followed by up to 5 phone calls (including evenings and weekends). After surveying the first validated control for each REP donors, we will prioritize surveying controls for donors who lack completed surveys by a matched control.

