### Limitations of prior work

In a review of studies reporting increased long-term risk for LDs, Janki et al. identified that both the Norwegian study reporting an increased risk of CVD, mortality, and ESKD, and the US study reporting increased risk of ESKD, selected non-donor control populations that were healthier than the donors, resulting in an over estimation of risk [103]. In addition, the definition of ESKD differed between donors and non-donors in the US study, potentially biasing the results. A meta-analysis of the cardiac studies concluded that there was no increase in CVD disease or mortality in LDs [104]. For the two studies identifying an increased risk of ESKD among LDs, the number of events was small, and there have been additional concerns about methodology, including: controls were non-contemporaneous and from a different geographic location; lack of renal function assessment for controls at the date corresponding to the date of donation; and concerns about the choice of statistical methods [105–115].

A key limitation in existing studies is that there was no determination of family history of chronic kidney disease (CKD) or ESKD for controls. In the Norwegian study, all 9 donors who developed ESKD were first-degree relatives of the recipient; in the US study, 83 of the 99 who developed ESKD were related to the recipient. Numerous studies in the general population have shown that individuals related to a person with ESKD have an increased risk of ESKD [116–122]. Wainright et al., using the Organ Procurement and Transplantation Network (OPTN) database, reported that LDs who were first-degree relatives of the recipient had significantly increased risk of ESKD (highest in identical twins) compared to LDs who were distant relatives or were unrelated to the recipient [123].

There have only been a few studies of pregnancy risk postdonation [100–102, 124, 125]. Studies have been limited by low numbers of events, and the design has generally been restricted to a before-and-after study design which may result in an over estimation of risk.

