## Methods

### Overview of study design

This is a matched cohort study of LDs from UMN and Mayo Clinic with contemporaneous, chart-validated, healthy matched REP controls with an index date (date of donation for LD) between 1963 and 2012. This time frame was chosen since the focus of the study is on long-term (> 10-year postdonation) outcomes (see Fig. 1). New outcome data will be ascertained from national registries, including the National Death Index (NDI, mortality), United States Renal Data System (USRDS, ESKD), and a new survey of health outcomes. The new data will be augmented with information collected from prior surveys (UMN LDs) and medical record review (UMN LDs and REP controls). Study criteria for donors includes: 1) provided research authorization and 2), US residency. Known non-US residents will be excluded from donor and control cohorts since national database information is unavailable for these individuals.

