### Study cohorts

#### UMN LD cohort

From January 1, 1963 through December 31, 2012, there were 4022 LDs at UMN who met the study criteria. Most LDs were from the upper Midwest region of the US, and detailed descriptions of the UMN LD cohort have been published [45, 50]. At donation, laboratory and demographic variables, surgical information, and peri-operative course information is collected. Prior to 2003, LDs were surveyed intermittently. In 2003, all donors were contacted to be surveyed and asked to consent to be surveyed every three years. Since 2003, consenting LDs are surveyed postdonation at regular intervals (6, 12, and 24 months, and then every 3 years). Those not returning to the clinic are sent a survey (by mail; or, if preferred, by email) to determine health status. If the survey is not returned, the LD is contacted by phone monthly, for 3 months. At least one phone call is made in the evening and one on weekends to increase response rates. LDs are also asked to provide alternate contacts. For LDs who become lost to follow-up UMN uses these contacts to ask for a current phone number and address. Available internet search engines and other databases (e.g., Accurint.com, Peoplefinder.com) are also used to identify LDs lost to follow-up.

At each contact, LDs are asked about hypertension, DM, and other diagnoses requiring treatment. Female donors are asked about pregnancy history. LDs are also asked to provide recent lab test results and copies of medical records; alternatively, with LDs’ permission, UMN investigators contact local clinics for recent medical records that include clinical notes and laboratory test results, including serum creatinine, glucose, urinalysis, and urinary protein measurements. Those without recent information are asked to get a history, physical, and labs at their local physician’s office and have the results sent to UMN. For LDs willing to do the tests but without insurance coverage, UMN pays for them. A summary of the clinical and demographic characteristics of the UMN LD cohort is given in Table 1.

**Table 1 Tab1:** Characteristics of the University of Minnesota (UMN) and Mayo Clinic donors

	UMN donors (N = 4022)	Mayo donors (N = 3035)
Years from donation to last survey or History & Physical (mean ± SD)	22.04 ± 11.93	
No returned surveys	9.5%	
Sex (%)		
Female	2294 (57.0%)	1668 (55.0%)
Male	1728 (43.0%)	1354 (44.6%)
Unknown	0 (0%)	13 (0.4%)
Age at donation (mean ± SD)	39.02 ± 11.64	42.52 ± 11.98

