#### Mayo clinic LD cohort

Between 1963 and December 31, 2012, 3035 LD transplants were performed who met the study criteria, with most LDs from the upper Midwest region of the US. The acquisition and storage of all relevant clinical data for all LDs are currently available via the Transplant Center clinical databases, which interfaces with the institution’s electronic medical record to access laboratory and demographic variables, surgical information, and peri-operative course. The Mayo Clinic LD program provides an additional source of long-term LD follow-up that will: (a) increase the sample size to increase the statistical power for analyses of certain outcomes (ESKD and mortality) and (b) add a second site to assess the generalizability of findings. A summary of the clinical and demographic characteristics of the Mayo LD cohort is given in Table 1.

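### For the pooled ESKD and mortality analyses, only registry linkage is described for Mayo donors, while REP controls also get chart review and the new survey; no rule makes the event sources equal

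*Protocol article*

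**What the plan says.** **Why Mayo donors are included.** The section on the Mayo Clinic LD cohort says the second centre will "increase the statistical power for analyses of certain outcomes (ESKD and mortality") and will help to assess generalizability.

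**Registry linkage covers everyone.** Under National registries, identifiers "for the UMN and Mayo donors and the REP controls will be sent in a secure manner to the NDI and to the USRDS".

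**The added sources do not cover everyone.** The next two sections, on medical record review and on survey data, both name mortality and ESKD in their headings. They describe chart abstraction and a new survey for UMN donors and REP controls. The Overview of study design says the new data will be "augmented with information collected from prior surveys (UMN LDs) and medical record review (UMN LDs and REP controls"). The survey section gives reasons for leaving out Mayo donors, including that they were not routinely contacted after donation, and concludes: "Because of this and budgetary constraints, only the REP controls and UMN donors will be surveyed".

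**Table 2** has columns for UMN donors and REP controls and none for Mayo donors. For controls it lists chart review, study survey and USRDS for ESKD, and chart review, study survey and NDI for vital status. For UMN donors it lists donor survey (with chart review if available), study survey and the same registries.

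**Analysis.** Statistical analyses details puts donation centre into the model as a covariate whenever Mayo donors are included. It does not say which sources define a pooled event.

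**Claims about ascertainment.** The Discussion presents uniform event ascertainment as a strength and says that differential ascertainment bias will be avoided. Limitations of prior work faults an earlier study because "the definition of ESKD differed between donors and non-donors in the US study, potentially biasing the results".

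**The concern.** Take a control matched to a Mayo donor whose ESKD or death appears in the chart but fails to link to a registry. Under Table 2 that control has an event. A Mayo donor with the same history and the same failed link would, on the ascertainment described, stay event-free to the end of follow-up. The additional capture therefore works on one side of the Mayo matched sets, and on the two outcomes for which Mayo donors were added.

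Within those sets it pushes the donor-versus-control hazard ratio downward, towards the stated hypothesis of small and clinically insignificant differences. A centre covariate lets the baseline hazard differ between Mayo and UMN. It cannot repair a difference in capture between donors and controls inside the Mayo sets.

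**Working it through.** **1. Sources side by side (death and ESKD, after the index date)**

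| Group | NDI / USRDS | Chart review | Surveys |
|---|---|---|---|
| UMN donors | yes | if available | donor survey and new survey |
| Mayo donors | yes | not described | no |
| REP controls | yes | yes | new survey |

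The registries are the one layer common to all three groups.

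**2. The plan's mortality power figure depends on pooling.** Inputs from the cohort and Power sections: "there were 4022 LDs at UMN who met the study criteria", and at Mayo "3035 LD transplants were performed who met the study criteria"; 98% of donors matched; 11% mortality; 5% type-1 error (taken as two-sided); 80% power.

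- Donors: 0.98 × (4022 + 3035) = 6916.
- Schoenfeld: HR = exp[(1.960 + 0.842) / √(E·a·(1 − a))], where E is the number of deaths and a the donor fraction.
- 3:1: E = 6916 × 4 × 0.11 = 3043, a = 0.25, HR = 1.124.
- 1:1: E = 6916 × 2 × 0.11 = 1521, a = 0.5, HR = 1.154.
- With cohort-weighted mortality (donors 9.85%, controls 11%) the values are 1.126 and 1.159, which round to the stated 1.13 and 1.16.
- UMN donors alone at 11% give 1.17 and 1.21.

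The plan's figures reproduce, and they need the Mayo donors.

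**3. Mayo's share of donor deaths.** The Power section reports 12% of UMN and 7% of Mayo donors deceased: 0.12 × 4022 = 483 and 0.07 × 3035 = 212. The share is 212 / 695 = 30.6%.

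**4. Effect on the mortality hazard ratio.** Let s be the share of true events that the registries find, taken as equal in donors and controls. Let u and c be the all-source capture in UMN donors and in controls. With event counts driving the hazard ratio:

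- Mayo sets: factor = s / c. Because controls have the registries plus other sources, c ≥ s and the factor is at most 1.
- Pooled: factor ≈ (0.694·u + 0.306·s) / c.

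With u = c = 1 the pooled factor is 1 − 0.306 × (1 − s):

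| s (assumed) | Mayo sets | Pooled | True HR 1.13 appears as | Power at 3:1 |
|---|---|---|---|---|
| 0.98 | 0.98 | 0.994 | 1.123 | 79% |
| 0.95 | 0.95 | 0.985 | 1.113 | 72% |
| 0.90 | 0.90 | 0.969 | 1.095 | 59% |

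Without the bias, power at HR 1.13 with 3043 deaths is 83%.

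**5. The pooled sign is not fixed.** With s = 0.95 and u = 1, the numerator is 0.694 + 0.306 × 0.95 = 0.985. If control capture c is also 0.985, the pooled factor is 1. If c is 0.97, it is 0.985 / 0.97 = 1.015, and the bias runs upward.

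**6. ESKD.** The factor is 1 − m(1 − s), where m is Mayo's share of donor ESKD events, which the documents do not give. The headcount share (43%) with s = 0.90 would give 1 − 0.43 × 0.10 = 0.957. That m is probably too high. In Table 1, (1647 + 400) / 3035 = 67% of Mayo donations fall in 2000–2012, against (1200 + 229) / 4022 = 36% at UMN, and the Background says that ESKD accrues late after donation.

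**The case against.** The best case for the plan is that a registry-based endpoint for the pooled analyses is the natural reading. The Overview pairs NDI with mortality and USRDS with ESKD, the registry section covers all three cohorts, and Mayo donors are added for exactly those two outcomes. Table 2 is titled for UMN donors and REP controls, so it need not govern the Mayo comparison. Source hierarchy is also often left to an analysis plan. This has weight, but the document does not say it. The control sources that it lists for death and ESKD go beyond the registries, and the Discussion asserts uniformity without excepting Mayo donors. That assertion conflicts with the survey section whatever an analysis plan may add.

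Three stronger readings are tempting, and the documents do not support them:

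- **That registries are the only source of events in Mayo donors.** The Power section already reports 7% of Mayo donors deceased while linkage is still in the future, so some unnamed source of vital status exists. The Mayo cohort section mentions databases linked to the medical record, and the abstract and Outcomes section speak of record review of donors in general. Follow-up outside the registries is not described for Mayo donors; that is not proof that there is none.
- **That the event definition differs.** No different clinical definition of ESKD or death is stated. The difference lies in supplementary sources on top of a shared registry, so the parallel with the criticised earlier study is only partial.
- **That the pooled hazard ratio is certainly biased downward.** UMN donors are surveyed every three years with telephone tracing and alternate contacts. Their capture may exceed that of controls, which would push the other way.

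It is also fair that the survey adds little for deaths, since it goes to people not known to be deceased. Its listed items mention ESKD only as family history, although Table 2 counts it as an ESKD source. The extra source in controls is therefore mainly the chart.

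**Conclusion.** The point holds in a limited form. For death and ESKD, the ascertainment described for Mayo donors is narrower than that described for controls. No rule confines pooled events to the shared registries, and the Discussion's uniformity claim is not true of Mayo donors as the plan stands.

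If control events found only by chart or survey are counted, the hazard ratio within the Mayo sets is biased downward, assuming equal linkage sensitivity in donors and controls and no further Mayo source. The centre covariate leaves that in place. The pooled mortality factor of 0.97–0.99 rests on an assumed registry sensitivity of 90–98%, on full capture in UMN donors and controls, and on the deaths reported to date. At 98% the shift is negligible. At 90% it takes 1.13 to 1.095, about a quarter of the detectable excess (0.035 / 0.13 = 27%). The net pooled direction is not settled by the documents, and no factor can be fixed for ESKD.

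**What to change.** 1. In every ESKD or mortality analysis that includes Mayo donors, count an event only if it comes from USRDS or NDI respectively, in donors and controls alike, with one common registry end date.
2. Use deaths and ESKD detected by chart or survey only in a sensitivity analysis of UMN donors and their controls.
3. Report the share of control events found outside the registries. This estimates linkage sensitivity from data already being collected, provided that it carries over to donors.
4. Qualify the Discussion's paragraph on uniform ascertainment so that it describes the registry endpoints for all cohorts and the survey for UMN donors and controls only.

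No new data are needed. The cost is that control and UMN donor events found only by chart or survey leave the pooled analysis, in proportion to registry incompleteness. At 3:1 and 11% mortality there are about 3 × 6916 × 0.11 = 2282 control deaths, so about 46 would drop at 98% sensitivity and about 228 at 90%. The loss of precision is modest: even if all groups lost 10% of events, E = 0.90 × 3043 = 2739, and the detectable HR is exp[2.802 / √(2739 × 0.1875)] = 1.132 instead of 1.124.
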